### Intervention fidelity

To ensure both programs are delivered with expertise and fidelity, at least two of the three intervention trainers will be social workers from the field with experience in working with adolescents or families, who have completed the mandatory 3-day certified SFP 10–14 training program. The SFP-Mind facilitators will either be the program developers or facilitators trained by experienced personnel in teaching the novel mindfulness modules and require having personal experience with MT prior to starting the group trainings. This way, we aim for an adequate standard for MT delivery that is comparable to other mostly school-based MT approaches among universal youth populations [43, 71–74] and family-based approaches [65]. While we acknowledge the importance of mindfulness skills among trainers, our approach reflects externally valid conditions which might be found in real-world conditions, thus maximizing generalizability. Scripted manuals in both conditions support clarity, fidelity, and adherence, which will be monitored during the study. Specifically, two independent raters will estimate adherence in videotapes of selected sessions using a list of prescribed activities as applied in a previous study [34] and with modifications made for novel MT program content. Data on acceptability of the programs by the study participants and the facilitators will also be collected.

### Baseline assessments and follow-ups

Study outcomes for adolescents and their parents/carers will be assessed by trained research staff blinded to the intervention condition at the families’ homes. Participants will be surveyed at baseline (prior to randomization), post intervention (approximately 8 weeks after baseline), as well as 6 months and 18 months (follow-ups) after post assessment. Fidelity and adherence data (i.e., ratings of training sessions) will be gathered during the intervention period (7 weeks). Figure 2 shows an overview of measures from study participants at each time point.

**Fig. 2 Fig2:**
[figure not shown]
Standard Protocol Items: Recommendations for Interventional Trials (SPIRIT) diagram detailing trial activities and measures and their timing. 2D:4D second and fourth-finger lengths ratio, BSI Brief Symptom Inventory, CGT Cambridge Gambling Task, DERS Difficulties in Emotion Regulation Scale, IEM-P Interpersonal Mindfulness in Parenting scale, MAAS Mindful Awareness and Attention Scale, MBI-TAC Mindfulness-Based Interventions—Teaching Assessment Criteria, MID Monetary Incentive Delay, PRSQ Parental-Representation-Screening-Questionnaire, PSS-4 Perceived Stress Scale German Version, SDQ Strengths and Difficulties Questionnaire, SF-8 Short-Form Health Survey, SFP Strengthening Families Program, SFP-Mind Strengthening Families with Mindfulness, SST Stop-Signal Task, SURPS Substance Use Risk Profile Scale, TLFB Timeline Follow-Back

### Outcome measures

Most study outcome measures, including the data on substance use, are self-report questionnaire data, which will be completed either on paper or via tablets. Substance use data will not be biochemically validated. In our previous study [34] we verified the adolescents’ self-report data by analyzing their urine samples for cotinine (threshold 50 ng/ml), ethyl glucuronide (ETG; threshold 0.1 mg/l), and tetrahydrocanabinol carboxylic acid (THC carboxylic acid; threshold 10 ng/ml). We found that the level of underreporting was very low (0.4–14% for various substances) and therefore we generally expect valid self-report data on substance use in the forthcoming trial. Secondary outcomes include questionnaire data and experimental data measured with a comprehensive (neuro)behavioral test battery (see later). Details of the measures and the time points at which they will be collected are shown in Fig. 2 (also see Additional file 3 for the filled SPIRIT 2013 Checklist).

### Primary outcomes (adolescent-completed)

The primary trial outcome to estimate the effectiveness of the novel MT-extended prevention program will be adolescent drinking 18 months after the intervention (one adolescent per family will be included in the analysis). While other substances are also relevant, we consider a primary focus on alcohol to be adequate particularly because: Germany is a high-consumption country, with alcohol being the primary substance of abuse [5]; delay of alcohol use is considered a primary substance use prevention goal, since development of SUD has repeatedly been shown to be predicted by the age of drinking onset [13, 76, 77]; significant proportions of youth in Europe start drinking at levels that is harmful to their healthy development early in their lives [78]; and addictive developmental trajectories are typically characterized by early onset and rapid acceleration of drinking [79]. To assess drinking we will form an alcohol initiation index (AII) that consists of the following items: “Have you ever tried to drink alcohol (just a sip but not a full drink)?”; “Have you ever had a full drink of alcohol (more than just a few sips)?”; “Have you felt (minimal) drunk?”; and “Have you ever felt (severely) drunk?” All four items will be answered according to a binary yes–no format and coded as 1 for yes and 0 for no. Comparable index-based measures for lifetime substance use were used extensively in previous studies [80–82].

Accordingly, we will examine the four lifetime use items individually, but the primary outcome will be the sum of the scores of these lifetime use items at the 18-month follow-up. Inconsistencies in the reports of lifetime alcohol use will be corrected. In cases where a participant reports a lifetime use behavior at one data collection point but reports no such use at a later collection point, the later report will be corrected to reflect the previously reported initiation of that behavior. For analytic purposes, lifetime use measures will be adjusted to control for baseline use. These adjusted lifetime use measures, called new-user rates, indicate whether use was initiated since baseline. Prior studies have reported the validity of similar substance use indices [82, 83].

### Secondary outcomes (adolescent and parent-completed)

Additional drinking outcomes, such as frequency and quantity of alcohol and drug use other than alcohol within the past 30 days prior to assessment, will be included as secondary outcomes and assessed using the standardized, calendar-based Timeline Follow-Back (TLFB) interview format [84]. As MT can be expected to foster improvements in top-down control [38, 41–44], we focus on experimental measures of self-regulation as key secondary outcomes in this study. Although self-regulation is a multidimensional “umbrella construct” across different scientific disciplines [85], p. 2693, definitions typically include the inability to delay gratification, insensitivity to negative consequences, distractibility, and the inability to inhibit or control impulsive behavior [85–87]. To specifically assess self-regulation in this study, we use versions of the Cambridge Gambling Task (CGT) from the Cambridge Cognition Neuropsychological Test Automated Battery (CANTAB; Cambridge Cognition) as a measure of delay discounting [53], the Monetary Incentive Delay (MID) reaction time task to assess reward sensitivity [88], and the Stop-Signal Task (SST) that is a widely used index of impulse control [89, 90]. All of these tasks have been used in previous studies [53, 54] and will be adapted to the specific needs of the present trial.

Moreover, we will include a range of individual and family-level variables as secondary outcomes as indicators for risk or resilience in the developmental course of SUD and related difficulties. These outcomes (A indicates outcome is adolescent-directed, P indicates it is parent-directed) are as follows:
Social, emotional and behavioral functioning (SDQ—Strengths and Difficulties Questionnaire German youth version) [91] (A + P)Screening of mental problems (BSI—Brief Symptom Inventory) [92] (P)Mindfulness Skills (MAAS—Mindful Awareness and Attention Scale) [93, 94] (A + P)Health-related quality of life (KIDSCREEN-10) [95] (A)Short-Form Health Survey (SF-8) [96] (P)Stress (PSS-4—Perceived Stress Scale German Version) [97] (A + P)Emotion regulation (DERS—Difficulties in Emotion Regulation Scale) [98, 99] (A)Reward processing (Monetary Incentive Delay Task) [88] (A)Impulse control (Stop Signal Task) [89, 90] (A)Delay discounting (Cambridge Gambling Task) (CANTAB; Cambridge Cognition) (A)Impulsivity (SURPS—Substance Use Risk Profile Scale) [100] (A)Mindful parenting (IEM-P—Interpersonal Mindfulness in Parenting scale) [62] (P)Family functioning (Family APGAR) [101] (A + P)Parental-Representation-Screening-Questionnaire (PRSQ) [102] (A + P)Previous experience with mindfulness-related practices (e.g., meditation, yoga, etc.; purpose designed) (A + P)Prenatal androgen exposure: the second and fourth-finger lengths ratio (2D:4D) will be scanned and used as a proxy of intrauterine exposure to gonadal steroids, which is a covariate for addiction development [103] (A)

### Implementation outcomes

For the participants in the SFP-Mind group only, we will assess mindfulness practice using several questions about sustained use of mindfulness practice in the follow-up assessments. In both intervention groups, we will also assess the following variables:
Program satisfaction: participants (parents and adolescents) will rate how satisfied they are with the program based on the Treatment Satisfaction Questionnaire (*Fragebogen zur Beurteilung der Behandlung*, FBB) [104] (A + P)Trainer adherence to principles and concepts of mindfulness will be rated according to a purpose-designed rating scale based on the MBI:TAC (Mindfulness-Based Interventions—Teaching Assessment Criteria) proposed by Crane et al. [105]Ongoing mindfulness practice (formal (e.g., meditation of deep breathing) and informal mindfulness practices; purpose designed; analysis of home practice diary and evaluation of frequency of app use) (A + P)

### Sample size

Development of the intervention is part of the ongoing study; thus, the empirical base for calculation of expected intervention effects is limited at the outset. However, the power calculation was based on our prior SFP 10–14 evaluation [34] and current evidence for MT in youth [42, 43]. Based on this research, we expect a small to medium effect size (ES) of *d* = 0.40 for the primary endpoint at 18-month follow-up in favor of SFP-Mind over standard SFP in a two-group analysis of covariance (ANCOVA). A sample size of *n*_1_ = *n*_2_ = 91 (total *n* = 182 families) is sufficient to detect effects of this size with a statistical power of 80%, a two-sided α level of 5% (estimated with PASS 15; NCSS, LLC, Kaysville, UT, USA) (ANCOVA), and an assumed correlation of *r* = 0.30 between the baseline and the follow-up measurements. Based on our previous SFP 10–14 trial [34] we expect a loss to follow-up (after 18 months) of 15%, and will therefore oversample by this percentage (total *n* = 216 families).

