### Randomization procedure and blinding

Enrolled families will be randomized in a 1:1 allocation ratio into both intervention groups (SFP or SFP-Mind), as per a computer-generated randomization schedule stratified by recruitment center and intervention cycle. Multiple recruitment centers will be used for the trial. As soon as there are sufficient consenting participants for a single intervention cycle of seven sessions (typically six to eight families per intervention arm), the following random allocation process will be applied. First, an independent statistician will be informed by the study team about the sample size of participating families in the designed intervention cycle and create a concordant computer-generated randomization sequence, which will be concealed until assignment occurs. Second, a researcher independent to the study team will receive an anonymized index identification code for each family participating in that intervention cycle, including information on absolute time restrictions for participation (i.e., holidays, carers’ weekday absences), from the study team. The independent researcher will then randomly assign an index identification code to the randomized sequence. In the case that a defined time restriction of one family means incompatibility with the randomly allocated intervention timing, the family will be allocated to the other intervention arm by the independent researcher. This methodology is necessary to ensure family participation as some might have fixed time constraints to participate. In the event of reallocation due to individual time restrictions, the index identification code will be separately reported to the study team after the allocation process is finalized to allow for methodological scrutinization. See Additional file 2 for a flow chart of randomization procedures.

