### Interventions

#### SFP 10–14 (control)

Families in the control group will participate in the standard SFP 10–14, which is a highly structured and evidence-based prevention program for families at the universal prevention level [27]. ›*Familien stärken*‹ is the certified German version, which relies on a video/DVD-based approach to learning the same as the original US program. In the narrated videos, participants see typical family interactions in diverse families and settings. To accommodate a contemporary urban setting and to increase authenticity and credibility, in extensive pilot work the original US-version video material was presented and discussed in focus groups of target families and translated as well as culturally adapted [68]. The program features seven weekly sessions of approximately 3 h. Per session, three group facilitators simultaneously work with 8–12 families, with parallel sessions for parents and adolescents during the first hour and sessions for the entire families during the second hour. All sessions include DVD presentations, role-plays, group discussion, input, social bonding, and skill-building activities. At the end of the program, a family meal is also provided to strengthen support and sharing between families. For more information on program content, see Bröning et al. [69].

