### Analysis plan

Analyses are planned and supervised by the trial statistician (AD). Study eligibility and enrollment will be summarized according to the CONSORT statement [106]. Descriptive statistics of baseline variables will be assessed by intervention arm. Analyses will be based on the intention-to-treat population, thus including data from all participants who provide baseline data and are subsequently randomized to one of the two trial conditions. Missing follow-up data will be imputed using multiple imputation methods. For the primary analysis, a mixed, linear, repeated-measurement ANCOVA will be conducted, with alcohol initiation (in the form of an initiation index) as the dependent variable; group, time, and interaction between group and time and recruitment center as fixed effects; baseline scores of alcohol use as covariates; adolescent and intervention groups within the study arm as random effects; and time as a repeated effect. The contrast between both groups at the 18-month follow-up will be assessed in a confirmatory manner. We will report adjusted group differences with corresponding 95% confidence intervals (CIs), *p* values, and Cohen’s *d* effect sizes. A systematic examination of factors associated with loss to follow-up will be conducted. The two-sided type I error will be set at 5%. An additional analysis will be conducted on a per-protocol data set as sensitivity analysis. A further sensitivity analysis will be carried out using the data set with all available cases (without any imputation of missing data). The secondary outcomes as well as a potential moderating role of individual and family-level variables and adherence to the intervention and engagement in home practice will be examined in an exploratory manner with appropriate methods. The other model parameters will be set as in the primary outcome analysis. The safety endpoints will be determined using frequency tables and, if possible, using mixed logistic regressions to compare the event frequencies. Interim analyses are not planned. A detailed statistical analyses plan will be prepared and finalized before the code is broken. Statistical analyses will be carried out with SPSS Version 23 or newer (IBM Corp., Armonk, NY, USA).

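### The stated 80% power is calculated for independent families, while the primary model has a random effect for program group, so it holds only if the within-arm group correlation is about zero.

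*Protocol article*

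**What the plan says.** The Sample size section gives a complete calculation. It states "we expect a small to medium effect size (ES) of *d* = 0.40 for the primary endpoint at 18-month follow-up", the advantage being for SFP-Mind and the method an ANCOVA comparing the two arms. The test has "a two-sided α level of 5"%, and the calculation takes "an assumed correlation of *r* = 0.30 between the baseline and the follow-up measurements". From this it concludes that 91 families per arm (182 in total) "is sufficient to detect effects of this size with a statistical power of 80"%. The increase to 216 is attributed to an expected 15% loss to follow-up. No group size, ICC or design effect appears.

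Three other sections bear on that figure:

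- Analysis plan: the model for the confirmatory 18-month contrast has "adolescent and intervention groups within the study arm as random effects", with recruitment center as a fixed effect.
- Randomization procedure and blinding: families are randomized individually, and a cycle starts once enough have consented, "typically six to eight families per intervention arm".
- SFP 10–14 (control): in each session "three group facilitators simultaneously work with 8–12 families".

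**The concern.** Families who attend seven sessions together, with the same facilitators and peers, may have outcomes that resemble each other more than those of families in other groups of the same arm. The analysis allows for this through the group random effect, but the power calculation sets it to zero. The two parts of the plan therefore describe different models, and the 80% belongs to the one that will not be fitted.

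This contrast is the trial's only confirmatory test, and it is made against an active program. If it is null, readers will weigh the result against the planned power. If that power was materially below 80%, the null result says less about an effect of d = 0.40 than the article implies.

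**Working it through.** **Inputs from the article.** d = 0.40; r = 0.30, so the residual variance factor is 1 − 0.30² = 0.91; two-sided 5%; 91 analysable per arm; 15% loss; 216 randomized (108 per arm); 6–8 families per group (trial recruitment per cycle) or 8–12 (program description).

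**Assumed inputs.** ICC from 0.01 to 0.10, taken on the baseline-adjusted scale, because the article gives none. The degrees-of-freedom (df) method is not fixed in the article, so both ends are shown.

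**Step 1: reproduce the stated figure.** For independent families the noncentrality is d / √(0.91 × 2 / n), and power comes from the noncentral t with 2n − 3 df.

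- n = 90: power 79.9%
- n = 91: 0.40 / √(1.82 / 91) = 2.828, power 80.3%

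So 91 is the smallest independent-families size that reaches 80%.

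**Step 2: look for a reserve.** 182 / 0.85 = 214.1, against 216 stated. 216 × 0.85 = 183.6, or 91.8 per arm, which gives 80.7%. By interpolation, exactly 80% needs about 90.3 per arm, so the design effect that can be absorbed is 91.8 / 90.3 ≈ 1.017. With individual-level df, that is used up at an ICC of about 0.003 (8 per group) to 0.004 (6 per group).

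**Step 3: power with clustering.** With g families randomized per group:

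- analysed group size m = 0.85 g
- design effect DE = 1 + (m − 1) × ICC
- noncentrality = 0.40 / √(1.82 × DE / 91.8) = 2.841 / √DE
- groups per arm K = 108 / g
- df = 2K − 2 (group level) or 2 × 91.8 − 3 = 180.6 (individual level)

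Example, g = 8 and ICC 0.05: m = 6.8; DE = 1 + 5.8 × 0.05 = 1.29; noncentrality = 2.841 / 1.136 = 2.501; K = 13.5, so group-level df = 25. Power is 67.2% with 25 df and 70.1% with 180.6 df.

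| ICC (assumed) | 6 per group: group df / individual df | 8 per group: group df / individual df | Range |
|---|---|---|---|
| 0.01 | 77.2% / 79.1% | 75.6% / 78.4% | 76–79% |
| 0.02 | 75.6% / 77.5% | 73.4% / 76.3% | 73–78% |
| 0.05 | 71.0% / 73.1% | 67.2% / 70.1% | 67–73% |
| 0.10 | 64.2% / 66.3% | 58.4% / 61.3% | 58–66% |

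**Step 4: detectable effect.** Solving the same formula for d at 80% power and ICC 0.05 gives about 0.44 (6 per group, individual-level df) to 0.47 (8 per group, group-level df).

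**Step 5: the other group size.** At ICC 0.05, 12 per group gives 59.8% (group-level df) to 64.8% (individual-level df). With 8 per group as above, the range for 8–12 is about 60–70%.

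**The case against.** The strongest reply is that the shortfall rests on an ICC that the article does not give. Families are randomized individually, and center is a fixed effect, so likeness due to center is largely removed from the contrast. What counts is variation between groups within an arm that arises after allocation and still shows 18 months later on a lifetime-initiation index. That may be small, and an ICC that included center variance would overstate the loss. This stands as a reason to make the size conditional: at ICC 0.01 the loss is only a few points. It does not remove the mismatch, because neither individual randomization nor the center effect eliminates variance between groups within an arm, and the plan itself fits a term for it.

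A second reply is that the planned test already models the group, so the omission from the power statement does not by itself invalidate the test or its confidence interval. That is right; the fault lies in the power claim. Uncertainty about d also matters as much: at d = 0.35 with 91 independent families per arm, the noncentrality is 0.35 × √(91 / 1.82) = 2.475 and power is about 69%.

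Third, the 8–12 families come from the description of the standard program, whereas 6–8 describes recruitment per cycle in this trial. The two overlap at 8 and may describe different things. So 8–12 is a side scenario, not the trial's stated plan.

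The absence of the full analysis plan is not an answer. The article states a finished calculation, and a later document cannot make 91 per arm yield 80% under the group model once the ICC is more than trivially positive.

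**Conclusion.** The power statement needs correction. The sample size is arithmetically right for its own inputs, but those inputs describe independent families and not the planned primary model, and there is virtually no allowance for clustering. At the assumed ICCs from 0.01 upward, with 6–8 families per group, power falls below 80%: slightly at 0.01, and by roughly 7 to 13 points at 0.05.

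Three stronger readings are not supported:

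- A reader might infer that the trial's power simply is 60–75%. That depends on an ICC that the article does not supply.
- A reader might infer that power falls short even at ICC zero, at about 78–79% with 6–8 per group. That follows only if group-level df are imposed, and the plan does not fix the df method; individual-level df give 80.7%.
- A reader might treat 8–12 families as the trial's group size and take 60–70% at ICC 0.05 as its power. The article does not settle that.

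**What to change.** Keep 216 families and the planned analysis. Restate the power and the effect detectable with 80% power for the model with the group random effect, using a design effect of 1 + (m − 1) × ICC or a simulation of the model. Take the within-arm group ICC from the sponsor's earlier SFP 10–14 trial, which already informs the effect size and the dropout rate, if those data allow it. Otherwise tabulate ICC 0.01 to 0.10. State the df method. Reconcile the group sizes in the randomization and program sections so that one range feeds the calculation.

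This takes one paragraph in the protocol or analysis plan. It needs no extra families and no design change; the only cost is a less favourable stated power.
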